**Follow-up assessments**

As part of the retention strategy, study staff will contact participants by mail, phone, email, and social media messages to remind them of upcoming appointments or to reschedule missed appointments. Participants will be informed during the consent process that we may visit them at their home, work or other location where they may be found if we are unable to contact them by phone or mail. Study staff will use contact information provided by the participants to get in touch with them.

***Monthly contact by phone/in-person***

1. To enhance retention in the study, study staff will conduct monthly check-in phone calls or visits with all study participants to update locator and contact information and provide an opportunity for individuals in the texting intervention group to customize the frequency and content of their text message for the next month (including reminders for the next medical appointment, ART dosing, and prevention plan goal). In addition, participants will be asked about HIV medication adherence for that past month (See Appendix N: Monthly call Script and Medication Adherence Tool) to help validate self-reported adherence at the 12-week and 24-week in-person assessments. Study staff will also remind study participants about the next monthly call date and next study appointment date. A $10 incentive in the form of an American Express Gift Cheque will be provided for each successful monthly contact, and participants can opt to receive the incentive at that visit (if in person), arrange for another date/time for pick-up (if by phone), or receive their bundled incentives at the next study visit.

***Study Visit 2 (12-week in-person assessment) and Study Visit 3 (24 week in-person assessment) (+/- 8 weeks):***

1. The study team will confirm and update locator information and will obtain updated medical release forms at Study Visits 2 and 3 from all participants to access medical records from community clinics and correctional facility at which the participant has received care during the follow-up period (See Appendix K: Medical Records Release Forms). Specific measures that will be abstracted from the medical records include data from the follow-up period (up to 32 weeks) related to HIV clinical care, comorbidities and sexually transmitted infections, and ancillary services.
2. Participants will self-report linkage to HIV care (date(s) and location(s)) and complete a follow-up CAPI.
3. A trained phlebotomist will conduct an intravenous blood draw in which up to 20ml of blood will be drawn for plasma viral load (PVL) testing, CD4 cell count (at baseline only) and back-up specimen storage. ART resistance and tests for other related co-morbidities may be conducted on stored specimen if funding is available. The specimen will be labeled with a study ID number only.
   - - - 1. The blood specimens for plasma viral load will be processed at the GWU Jordan virology lab and spun down twice at 1600 x g for 15 minutes, aliquoted in 2.2 ml aliquots (minimum volume) and frozen at -70 to -80C within 6 hours of collection. Specimens will be labeled using freezer labels with study ID, date, study name, visit number, and specimen type (EDT PL). All specimens will be banked at the Jordan lab at GWU until required for shipping and/or testing.
         2. Specimens for viral load testing will be shipped on dry ice to Miriam Hospital bi-weekly where they will be evaluated using PCR. Viral load reports using only study ID will be sent to study staff at Miriam Hospital, who will in turn send the results to GWU study staff via secure server and/or FedEx.
         3. Specimens for CD4 cell count will be processed and sent to a local lab for testing. The specimen will only be labeled with a study ID and results will be sent to study staff via a secure web portal and/or FedEx.
         4. The results of these tests will be shared with study participants upon request, and study participants may share the results with their health clinics or medical providers if they wish to do so.
4. At the end of the study visit the staff will provide a list of referrals, a $50 incentive for completion of the visit, $10 incentives for every successful monthly phone call since the previous study visit, and a voucher for transportation. The incentives will be in the form of American Express Gift Cheques.
5. After the study visit, the study staff will confirm the participant’s engagement in care by contacting his/her medical provider and obtaining data on appointments, plasma viral load, CD4 data if available and antiretroviral medication prescriptions, given approved medical release from the participant.

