- Detainees or recently released ex-detainees who meet the eligibility criteria will be offered the opportunity to participate in the study. Participation will be voluntary. Detainees who do not meet eligibility criteria or choose not to participate will return to their previous location as determined by the security staff. The standard of care for HIV discharge will not be affected by their refusal to participate.
- Detainees or recently released ex-detainees who elect to participate will complete written, informed consent for study participation with the study research assistant (RA). The informed consent form will be read aloud to the participant (see Appendix D: Informed Consent Forms). A copy of the informed consent will be provided to the participant. For participants recruited inside the DC DOC facilities, the GWU RA will provide the option of leaving their copy with the RA in order to protect confidentiality and receiving it at their next study visit after being released to the community. The RA will maintain a file of completed informed consents at the administrative study office at the Department of Epi/Bio at GWU in a locked file cabinet.
- Consenting study participants will also be asked to provide consent for release of medical records from the DC DOC facilities and any community medical providers that they may come into contact with during the course of the study.
- A study locator form requesting contact information for participants after release in the community will be completed. In the case of recently released ex-detainees the locator form will include participants’ current and anticipated contact information.

For community-recruited individuals, the baseline visit will occur within one study visit as much as possible. However, for individuals recruited inside correctional facilities, the baseline visit may be split across multiple time points if necessary, as determined by constraints of that facility.

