Linkage to care content: Text messages will be sent to remind the participant about his/her upcoming HIV appointment in the community. In addition, the message will ask the participant to contact their provider if s/he anticipates difficulty in attending the scheduled appointment. We will ascertain the participant’s next appointment during the monthly check-in phone call in order to set up or adjust the reminder text message. The participant will choose from pre-scripted appointment reminders or, if technically feasible, will create a customized message. The linkage message chosen by the participant will be recorded by the staff member.

- Pre-scripted text message example: “Don’t forget your upcoming Unity appointment. Call the clinic at 202-XXX-XXXX if you can’t make it”.
- Customized text message example: “Don’t forget your upcoming meeting at Church. Call the pastor if you can’t make it”.

Message reminders will be sent out at pre-determined intervals (e.g., weekly in the month before the appointment and then more frequently during the week of the appointment). Changes to text message content (pre-scripted or customized) will be recorded by the RA and will be entered into the SMS database.

A query message will be sent the day after the scheduled appointment and will ask “How did your appointment go? If OK, reply 1. If not OK, reply 2.” If the participant replies “1”, no further action will be taken. If the participant replies “2”, or if the participant does not respond to the query message within 24 hours, a study staff member will call the participant on their cell phone to assess barriers to care and the staff member will provide referral information (clinic, social work, case management) as needed. Responses to these texts and action taken by study staff will be recorded by the RA and then entered into the SMS database.

Adherence to ART content: For participants prescribed ART at the time of the baseline visit 3, text message reminders will be sent to remind the participant to take his/her ART. The participant will choose from pre-scripted ART medication reminders or, if technically feasible, will create a customized message. The ART adherence message chosen by the participant will be recorded by the staff member.

- Pre-scripted text message example: “Don’t forget your medications today. They are important!”
- Customized text message example: “Don’t forget to eat skittles today. They are important!”

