The longitudinal nature of the study (containing a baseline assessment before intervention and two follow-up visits after jail release) will result in repeated assessments of primary outcomes (plasma viral load suppression at Visits 2 and 3) and secondary outcomes (e.g., proportion linking to community HIV care at 30 days, 60 days, 90 days, etc.). These outcomes will be analyzed in the unified framework of generalized linear models (GLMs) with appropriate link functions (logit for dichotomized outcomes, e.g. linkage to care, detectable PVL; identify link for continuous outcomes, e.g. log-transformed PVL; or log link for count outcomes, e.g. # of non-main sexual partners). The setup of GLMs involves relating the expected outcome to a linear function of explanatory covariates, where the explanatory covariates will include a dummy variable encoding the treatment (=1) versus control (=0), dummies for study site and gender, relevant demographic covariates, and their interactions. Depending on the analysis objectives, three GLM model structures will potentially be used: 1) *Marginal models* will be used to analyze population-level intervention effect. Within-individual correlation of repeated measures will be accounted for using Generalized Estimating Equations (GEE),^6,7^ which yields consistent parameter estimates and robust standard error estimates. 2) *Random-effect generalized linear models* will be used to estimate the intervention effect at the individual-level.^8^ For those outcomes with only one follow-up visit, the model will be estimated using conditional logistic regression for binary outcomes or difference-on-difference regression for continuous outcomes for better estimation efficiencies. 3) *Markov transition models* will be used to investigate the intervention effect on the individual behavior change as previously conducted by this group,^9^ and includes the prior history of the outcomes as regression covariates; therefore, the transition model emphasizes more the effect of the intervention on outcome changes given the prior value of the outcome. Using these model setups, we will examine the different aspects of intervention for SA2 and SA3. These models will also allow us to quantify the differences between the two study sites and differences between male and female by testing the interaction between study arm and site, and potentially the interaction between study arm and gender.

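### Follow-up linkage to care is obtained only through attendance at Study Visit 2 or 3, so a participant who misses both has no written route to this secondary outcome

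*Protocol*

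**What the plan says.** The Analysis Plan names as a secondary outcome the "proportion linking to community HIV care at 30 days, 60 days, 90 days, etc".

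The follow-up procedures that produce it are listed under Study Visit 2 (week 12) and Study Visit 3 (week 24), each with a window of 8 weeks either side:

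- **Item 1:** medical releases are updated at the visits, and records are abstracted, including "data from the follow-up period (up to 32 weeks) related to HIV clinical care".
- **Item 2:** "Participants will self-report linkage to HIV care (date(s) and location(s)) and complete a follow-up CAPI".
- **Item 5:** "After the study visit, the study staff will confirm the participant’s engagement in care", by asking the provider for appointment data, subject to an approved release.

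The Screening and enrollment visit section already asks for a records release from correctional facilities and from "any community medical providers that they may come into contact with during the course of the study".

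Between visits, the Linkage to care content of the text-messaging intervention has staff learn the next appointment at the monthly check-in. Then: "A query message will be sent the day after the scheduled appointment". A staff call follows an unfavorable reply or no reply. The section on monthly contact, which applies to both arms, lists locator updates and medication adherence but no question on linkage.

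**The concern.** The trigger for measuring linkage is attendance at a study visit. People who have fallen out of care after release are plausibly also the people who miss study visits, so the outcome would tend to be missing where non-linkage is most common. The Study Termination section itself accepts that some participants will not return for every visit.

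The release, the abstraction form and the staff needed to look up appointment records without a visit already exist, but nothing in the protocol directs that use. Data that could be had would be lost.

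There is also a risk of unevenness between arms. Only the intervention arm is documented as giving staff appointment dates between visits, so the clinics known to staff, and hence the records they can request, may differ by arm.

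**Working it through.** **1. The plan's own figure.** Visit 3 at week 24 plus 8 weeks gives 32 weeks, or 32 × 7 = 224 days. This agrees with the 32-week limit stated for record abstraction.

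**2. Visit windows, in days from the visit clock's start.**
- Visit 2: nominal 12 × 7 = 84; window (12 − 8) × 7 = 28 to (12 + 8) × 7 = 140.
- Visit 3: nominal 24 × 7 = 168; window (24 − 8) × 7 = 112 to 224.

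**3. Does a visit on that day reach the endpoint day?** (Assumes linkage days and visit days share day 0.)

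| Endpoint | Visit 2, day 28 | Visit 2, day 84 | Visit 2, day 140 | Visit 3, day 112 |
|---|---|---|---|---|
| 30 days | no | yes | yes | yes |
| 60 days | no | yes | yes | yes |
| 90 days | no | no (6 days short) | yes | yes |

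The Visit 2 window has 140 − 28 + 1 = 113 days. Of these, days 28–89 (62 days, 62/113 = 55%) precede day 90, and days 28–59 (32 days, 32/113 = 28%) precede day 60. These are shares of calendar days, not of participants.

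**4. The common day 0 is an assumption.** The Analysis Plan does not state the origin of the 30, 60 and 90 days. If a jail-recruited participant's 12 weeks run from a post-release visit held 0 to 14 days after release, nominal Visit 2 falls on days 84 to 98 after release. It then reaches day 90 once the delay is 6 days or more. Visits for community recruits are counted from completion of baseline, which may be months after release. If linkage days run from release, Visit 2 may then fall well after day 90.

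**5. What is observed, by attendance pattern.**
- *Visit 3 attended:* dated self-report and records cover all three endpoints, whether or not Visit 2 took place.
- *Only Visit 2, on day 90 or later:* all three endpoints are covered.
- *Only Visit 2, before day 90:* someone already linked is known to be linked. Someone not yet linked has unknown status at the later endpoints unless provider records are obtained afterwards.
- *Neither visit:* no written procedure applies.

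**6. Possible size.** Let m be the share of an arm with no linkage data and p the linkage proportion among those observed. The arm's full proportion lies between (1 − m)p and (1 − m)p + m, an interval of width m whatever p is. The protocol gives neither m nor p. Assume m = 20% to 35% and p = 60%, with 150/2 = 75 per arm:
- m = 0.20: 0.20 × 75 = 15 participants; 0.80 × 0.60 = 48%, up to 48 + 20 = 68%.
- m = 0.35: 0.35 × 75 = 26 participants; 0.65 × 0.60 = 39%, up to 39 + 35 = 74%.

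**7. The missing-data plan.** The first analysis weights by a missingness model under an assumption conditional on baseline covariates. Being out of care after release arises after baseline, so these weights remove only the part of the selection that baseline covariates predict.

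**The case against.** Several points on the other side are sound.

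- **The 90-day endpoint is not lost.** From day 84 being before day 90, a reader might infer that the plan cannot capture 90-day linkage. It can: Visit 3 takes dated self-report at day 112 or later, and records run to day 224.
- **Missing one visit need not cost the outcome.** A reader might infer that linkage is unmeasured for anyone who misses a visit. Missing only Visit 2 costs nothing if Visit 3 is held. Visits may take place in a correctional facility after re-incarceration, and a final visit is sought from those who leave early. The baseline interview also has a domain on post-release contact with an HIV provider.
- **The window shares are not participant shares.** The 55% and 28% matter only where Visit 3 and later records are also absent.
- **A false treatment effect is not shown.** With attendance of 80% versus 65% and true linkage of 60% in both arms, counting unverified participants as not linked would give 48% versus 39%, a spurious 9 points. The protocol contains neither that rule nor those rates. It plans weighting followed by sensitivity analyses under missing-not-at-random models.
- **The arm imbalance is a risk, not a demonstrated scoring bias.** No section uses text replies to score linkage, and the text-message database is not among those listed for merging. For participants recruited in custody in both arms, facility staff supply community health referrals. The monthly call script is not shown.

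What remains is that no section directs ascertainment for a participant who misses both visits. The separately listed database on clinic appointment adherence has no described source, so it does not show that such participants are covered. The analysis methods soften the loss but do not recover the data.

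**Conclusion.** The point holds in a limited form. As written, follow-up linkage is tied to attending Study Visit 2 or 3. Participants who miss both have no written ascertainment, and those seen only at a Visit 2 before day 90 may lack 60- or 90-day status. The number affected cannot be derived from the protocol; the 15 to 26 per arm rests on the assumed 20% to 35% missing both visits. The direction of any bias rests on the plausible but untested premise that being out of care and missing visits go together.

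This concerns a secondary outcome; the primary outcome is viral suppression. It is worth correcting because linkage is half of the stated aim and the remedy is cheap. Whether records should outrank self-report is an endpoint choice that an analysis plan may settle, and is not part of this point.

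**What to change.** In the section on Study Visits 2 and 3 (items 1 and 5), state that:

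- for every randomized participant who has not refused or withdrawn records access, whether or not visits were attended, staff will request appointment records from the discharge-referral clinic and all known community providers under the enrollment release;
- this is done at one fixed time after day 90, for example at the end of the 24-week follow-up, by the same procedure in both arms;
- text-query replies and staff-call notes will not be used to score linkage.

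The cost is protocol wording and some extra record requests; the release, abstraction form and staff are already in place. Some clinics may ask for a newer signed release, and clinics unknown to staff will still be missed, so some dependence on attendance will remain.

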**Study Termination :**

Study participants may withdraw their consent to participate in this study at any time and for any reason. The site investigator may voluntarily withdraw from the study for any reason at any time. The site investigator may also withdraw participants from the study in order to protect their safety, or the safety of site staff and/or if they are unwilling or unable to comply with required study procedures after consultation with the co-PIs and Biostatistician. Participants also may be withdrawn if the study sponsors, government or regulatory authorities terminate the study prior to its planned end date. Participants will be informed in the consent process that the investigator or the study sponsor may terminate their participation in the study at any time without their consent for any of the reasons listed above. The study staff will explain the reason for terminating participants’ involvement in the study and what arrangements will be made for continued care.

The study staff will make every effort to enroll, follow, and obtain samples from all enrolled participants according to the study procedures listed above, while recognizing that each participant may not be able to return for all visits or undergo all protocol-dictated procedures.

Every reasonable effort will be made to complete a final visit with participants who terminate from the study prior to the end of the study period, and study staff will record the reason(s) for all withdrawals from the study in participants’ study records.

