***Baseline visit 2:***

Within 1 week of baseline visit 1, participants will complete baseline visit 2, which includes random assignment to the study arm, updates to the study locator information, and medical chart review. Depending on the operational time constraints in the facility and in the community GWU research space (some of which is rented from local CBOs), baseline visit 2 may occur immediately after the screening, consenting, and enrollment process, as determined by the facility or depending on time constraints at the GWU research clinic space.

For participants recruited in the community, a blood draw will be conducted to provide a baseline measurement of plasma viral load and CD4 cell count (baseline only) (see 12-week/24-week study visit section for description about blood draw). Study participants will be randomized at this point to either the 1) intervention arm or 2) the control arm. A 1:1 block randomization scheme will be created using a SAS program to select random assignments. Blocks of 4 will be used to ensure equal population of each group during the course of the study. The study coordinator will manage the randomization list. Prior to the visit, the RA will consult with the study coordinator for the randomized assignments. At the beginning of this visit with the participant, the RA will administer either the intervention (CARE+ Corrections tool) or the control condition to the participant based on their assignment.

- Intervention Arm:

Participants will complete the CARE+ Corrections counseling session, which will last less than 30 minutes. The CARE+ Corrections session will consist of the following:

- The CARE+ Corrections tool is a computerized, one-session motivational interview (for an outline of the CARE+ Corrections tool, see Appendix F: CARE+ Corrections Flow Chart and Excel Spreadsheet).

- The CARE+ Corrections session will be conducted using a laptop computer or tablet with a touch screen and consists of an audio-assisted session in which participants provide responses to questions about demographic characteristics, sexual risk behaviors and attitudes, substance use, mental health, and HIV treatment and adherence.
- After the computerized assessment is completed, the CARE+ Corrections tool will provide tailored feedback based on their responses to the above questions.

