Training on cell-phone intervention: All participants will receive training delivered by study staff on the cell phone intervention. This will include training on the use of the cell phone as well as how to view and respond to text messages. The staff member and the participant will practice sending and viewing text messages to confirm that the participant understands how to use the phone and text messaging. The staff member will review the text-messaging plans and the use of customized messages (as described below). To facilitate cell phone communication with community providers, the staff member will assist the participant with programming important phone numbers into the cell-phone for easy retrieval and use. Phone numbers will be obtained from the DC Ex-Offenders Returning Citizens Referral List (see Appendix M) and will include phone numbers for medical providers, community-based organizations, re-entry services, etc. The staff member will also review the lost cell phone policy (described below).

Cell-phone/SMS text messaging intervention content: Separate text messaging content will be used for linkage to care, ART adherence, and the promotion of the CARE+ Corrections prevention plan. Text-messages will be delivered through a contracted SMS provider. Participants will be asked to send a response to the text message within 24 hours when a study text message is received. For each content category, the participant will choose from pre-scripted messages or, if technically feasible, the participant will have the option of creating a customized message as described below. In addition, for each content category, the participant will be able to choose from several different text-message frequency options (such as daily, every other day, three times weekly, weekly). The frequency of text messages in each content category can subsequently be changed by the participant at the monthly check-ins according to preference. To maintain confidentiality, text messages will not contain participant names, mention of HIV infection or HIV medications, or specific providers that only provide HIV care.

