**Analysis Plan**

*Summary analysis:*

Demographic characteristics (including age, gender, ethnicity, etc.) and history of prior incarceration, sexual behaviors, drug and alcohol use, and medical history (including HIV testing history, HIV/HCV status) will be summarized using means/standard deviations, medians/ranges or counts/frequencies with corresponding 95% confidence intervals (CIs) as appropriate. The summaries will be stratified by arm. An intent-to-treat analysis will be used. Baseline characteristics will be compared between control arm and corresponding comparison arm using Pearson’s Χ^2^ test for categorical variables, student’s t-test for normally distributed or Wilcoxon’s test for non-normally distributed continuous variables to assess the success of the randomization procedure. Imbalances between the study arms will be documented and investigated. Imbalanced covariates will be adjusted for subsequently through regression analysis or weighted analyses. Lost-to-follow-up (LTF) and incomplete response will also be summarized by contingency tables for each arm stratified by gender and study site, and will be compared using Pearson’s Χ^2^ test to examine whether selection bias is induced by LTF. A diagram of LTF status will be created to summarize the disposition of participants at each study visit.

*Analysis of primary and secondary outcomes:*

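### Withdrawing participants from the study for non-compliance can cause avoidable, outcome-related loss of the 12- and 24-week viral load

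*Protocol*

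**What the plan says.** Study Termination (Protocol) allows the site investigator to withdraw participants for safety reasons, and also "if they are unwilling or unable to comply with required study procedures after consultation with the co-PIs and Biostatistician". Participants are told at consent that their participation can be ended on these grounds without their agreement. The section does not say which procedures count as required, sets no threshold, and does not distinguish ending study contacts or texts from ending outcome collection.

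The same section contains softer language. Staff are to try to follow and sample everyone, "while recognizing that each participant may not be able to return for all visits or undergo all protocol-dictated procedures". On early termination, "Every reasonable effort will be made to complete a final visit with participants who terminate from the study", and "study staff will record the reason(s) for all withdrawals from the study". The section on withdrawal under Data Transfer and Confidentiality adds that data gathered before withdrawal may still be used.

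The Analysis Plan states: "An intent-to-treat analysis will be used". The primary outcome is "plasma viral load suppression at Visits 2 and 3". Missing data are handled first by inverse probability weighting, under a missing-at-random assumption conditional on baseline covariates, and then by not-missing-at-random sensitivity models.

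No blinding is described. Under Baseline visit 2, "the RA will administer either the intervention (CARE+ Corrections tool) or the control condition to the participant based on their assignment".

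**The concern.** An intent-to-treat comparison needs outcomes on everyone randomised, whether or not they cooperated with the procedures. Here a post-randomisation behaviour is a discretionary ground for ending a person's time in the study. In this population, people who miss contacts and visits are plausibly also those who miss medication and have detectable virus, so the rule may act on a correlate of the primary outcome. Study staff deliver the arms, hear self-reported adherence every month and receive viral load results. Nothing in the text keeps a withdrawal decision independent of arm or outcome.

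The Analysis Plan itself warns that differential loss between arms could undo the randomisation. This rule lets the study add to that loss by its own decision. A separate SAP, which was not available, could say how withdrawn participants are analysed, but it could not supply measurements that were never taken.

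**Working it through.** The protocol gives no figure to reproduce. It states no significance level, power, expected suppression rate or expected withdrawal rate.

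**Step 1: do the stated safeguards close the gap?**
- *Final visit.* It is an effort, not a guarantee. The text does not say that it includes a blood draw or can stand as Visit 2 or Visit 3.
- *Visit window.* Visits 2 and 3 have a window of 8 weeks either side, so Visit 3 can fall from week 24 − 8 = 16 to week 24 + 8 = 32. A final visit before week 16 cannot serve as the 24-week measurement. One from week 16 could, if blood is drawn.
- *Records.* Consent to release of DOC and community records is sought at enrolment, and releases are updated at Visits 2 and 3. Provider confirmation follows a study visit. The text does not say that either continues after withdrawal.
- *Earlier data.* These are kept, but they do not replace a later outcome.
- *Weighting.* It conditions on baseline covariates, so it need not correct withdrawal that depends on behaviour during follow-up.
- *Not-missing-at-random models.* They address outcome-related loss directly, but by varying assumptions, not by recovering data.

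**Step 2: illustration of size.**

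From the protocol: up to 150 enrolled, allocated 1:1, so n = 150 / 2 = 75 per arm.

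Assumed: true suppression p = 50% in both arms (37.5 expected per arm); w people withdrawn from the intervention arm only; a fraction f of them unsuppressed; no outcome after withdrawal; analysis of those with data.

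Observed intervention rate = (37.5 − w(1 − f)) / (75 − w).

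| w | f = 1 (all unsuppressed) | f = 0.75 | f = 0.5 (same as the arm) |
| --- | --- | --- | --- |
| 4 | 37.5/71 = 52.8% (+2.8) | 36.5/71 = 51.4% (+1.4) | 35.5/71 = 50.0% (0) |
| 8 | 37.5/67 = 56.0% (+6.0) | 35.5/67 = 53.0% (+3.0) | 33.5/67 = 50.0% (0) |

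Differences are in percentage points against 50% in control. If the same withdrawals came from control instead, the signs would reverse.

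**Step 3: effect on false-positive risk.**

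Assume a two-sided 5% two-proportion z-test with pooled standard error. With 10% of the intervention arm withdrawn, all unsuppressed:
- n1 = 75 × 0.9 = 67.5; observed rate = 0.50/0.90 = 0.556; pooled rate = 75/142.5 = 0.526.
- SE = √(0.526 × 0.474 × (1/67.5 + 1/75)) = 0.084; shift z = 0.056/0.084 = 0.66.
- Rejection probability = 1 − Φ(1.96 − 0.66) + Φ(−1.96 − 0.66), about 10%.

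The same calculation with 5% withdrawn gives about 6%. If 75% of those withdrawn are unsuppressed, it gives about 5% (5% withdrawn) and 6% (10% withdrawn). Varying true suppression from 40% to 60%, with 10% withdrawn and all unsuppressed, gives a shift of +4.4 to +6.7 points and a type I error of about 8% to 13%.

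**The case against.** The strongest reply is that this is a retention-minded protocol and the clause is only a permission. Missed procedures are expected and tolerated, outreach is extensive, reasons for withdrawal are recorded, and nothing excludes withdrawn participants from analysis. All of that stands. It makes heavy use of the rule less likely, but does not say that outcome collection continues once the rule is used.

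Four stronger readings are tempting and are not supported:

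- *The rule does remove outcomes selectively and biases the result towards benefit.* The investigator may withdraw participants and need not. No rate is given, and the link with viral load is plausible but not shown in the protocol.
- *The intervention arm will lose more people because it has more procedures to fail.* Only that arm receives the texting intervention, in which "Participants will be asked to send a response to the text message within 24 hours when a study text message is received". The protocol attaches other consequences to failing these elements: an unanswered appointment query leads to a staff call, and a second lost phone ends the phone plan. It does not say that either counts as a required procedure for withdrawal. Arm-related loss is a possibility, not a prediction.
- *Anyone withdrawn before week 24 has no 24-week viral load.* With Visit 3 allowed from week 16, some will have one.
- *The biostatistician's part in the consultation is itself a flaw.* The protocol does not say that this role knows arm or outcome, and consultation may limit the investigator's discretion.

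**Conclusion.** The point holds as a weakness in how the protocol fixes withdrawal, and correcting it is a cheap improvement. The rule allows study participation, and with it outcome follow-up, to end on a post-randomisation ground that plausibly tracks the primary outcome. That works against the declared intent-to-treat analysis, and the stated safeguards only partly offset it.

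Its size is unknown. The +2.8 to +6.0 points for 4 to 8 withdrawals is the unfavourable end of an illustration. It rests on one-sided withdrawal, every withdrawn person being unsuppressed, no later outcome and no correction in analysis. The bias is zero if those withdrawn have the same suppression rate as the rest of their arm, and its direction depends on which arm loses whom.

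**What to change.** In Study Termination, remove inability or unwillingness to comply as a ground for ending study participation. State that such participants may stop texts or study contacts but remain in outcome follow-up unless they withdraw consent. That means the Visit 2 and Visit 3 blood draws if they are willing, and otherwise viral load and care visits from provider and DOC records under the existing releases. The Re-incarceration Plan already takes viral load from the facility record when blood is not drawn, so the route is familiar to the study.

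Leave the safety and regulatory grounds as they are, and keep the consultation with the co-PIs and Biostatistician.

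The cost is a change of protocol and consent wording, and a little more record abstraction for what is likely to be a small number of people.
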